### Confidentiality

The data safety monitoring board (DSMB) will be responsible for the preservation of data as well as the verification of data authenticity and correctness to ensure the accuracy of study results.

All participants will be identified using a reference number that will be used for the entire duration of the study. All data are needed to be strictly secured during transmission as well as archiving to ensure patient privacy and prevent data leakage or loss. All information that contains names or other personal identifiers, such as locator forms and informed consent forms, will be stored separately from study records identified by number, and contact information should be left after obtaining the family’s consent for the subsequent follow-up study, if any. The participant information materials and informed consent form are available from the corresponding author on request.

All data need to be kept for at least 3 years after the completion of the trial.

### Statistical methods

All efficacy analysis will be conducted on an intention-to-treat basis. The SPSS version 26.0 (SPSS, Chicago, IL) software will be used for statistical analysis. Clinical characteristics of infants will be described as mean with standard deviation or median with range for continuous variables and rate or percentage for categorical variables. Absolute risk differences with 95% confidence intervals (CIs) between VTV and PCV will be calculated for binary outcomes, and odds ratios with 95% CIs will be estimated by univariate logistic regression, followed by multivariate logistic regression if the prespecified baseline characteristics are unbalanced between the two groups. Absolute mean differences with 95% CIs (using *t*-test) or mean differences with P25-P75 (using Hodges-Lehmann) will be also calculated for continuous outcomes, and adjusted differences will be estimated by multivariate liner regression if needed. A *P* value < 0.05 was considered statistically significant.

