### Study design

A single-center randomized controlled trial will be performed. Patients will be randomized in two parallel groups: VTV vs PCV in 1:1 ratio. The study type was a superiority study to verify the use of VTV over PCV in VLBW infants.

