### Sample size

An RCT of VLBW infants with respiratory distress syndrome(RDS) receiving VTV or PCV as their primary respiratory support mode showed that the BPD/death rate of 26% and 64% respectively [15]. Based on this study, a sample size of 31 in each group will have 90% power to detect statistically difference at a 0.05 tow-sided significance level (MedSci, Shanghai, China). Considering a 20% of patients may withdraw from the research, a sample size of 68 will be appropriate.

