## Assignment of interventions: allocation

Randomization will be immediately performed once the eligibility is confirmed. All eligible infants will be randomized and assigned to either VTV or PCV group with 1:1 ratio. Stratified randomization will be done according to a computer-generated random number and variable block sizes (2) will be used to strengthen allocation concealment. Multiple birth infants will be randomized separately. Randomization will be stratified by birthweight (< 1000 g versus > / = 1000 g).

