### Primary outcome

Death or BPD at 36 weeks’ postmenstrual age will be used as the primary outcome. BPD will be diagnosed by clinical physicians. The definition and diagnostic criteria of BPD is according to NIH 2018 [16]. We have chosen “death or BPD (36w)” as our primary outcome to maintain similarity with previous trial comparing VTV and PCV [10].

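### Randomisation is stratified by birthweight, but the stated primary analysis leaves the stratum out, and the imbalance rule will almost never bring it in

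*Protocol article*

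**What the plan says.** The Primary outcome section makes the endpoint binary: "Death or BPD at 36 weeks’ postmenstrual age will be used as the primary outcome". The allocation section states: "Randomization will be stratified by birthweight (< 1000 g versus > / = 1000 g". It also gives a block size of 2.

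The Statistical methods section of the protocol article then sets out the analysis of binary outcomes. A risk difference with 95% CI and an odds ratio from a one-variable logistic model are always produced, "followed by multivariate logistic regression if the prespecified baseline characteristics are unbalanced between the two groups". The section gives no criterion for imbalance and does not say which estimate leads when both models have been run. Birthweight group enters the stated analysis only through the additional analyses, as a subgroup factor with an interaction test.

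**The concern.** A factor used to stratify randomisation should normally be in the primary analysis. Stratifying removes the between-stratum part of the chance difference between arms. An analysis that ignores the strata still counts that part as noise, so its test is conservative and power is lost.

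The conditional rule works against this. It selects covariates by how unequal they look, whereas the stratum matters because of how strongly it predicts outcome, and randomisation has already made it equal. In a trial of 68 infants precision is scarce, and the variable is known for every infant at entry. There is also an ambiguity: if the adjusted model is run, the plan has two results for its primary outcome and no stated order between them.

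**Working it through.** **1. The plan's own figure.** Inputs from the Sample size section: the reference trial "showed that the BPD/death rate of 26% and 64% respectively" (VTV, PCV), and "a sample size of 31 in each group will have 90% power to detect statistically difference at a 0.05 tow-sided significance level". With unpooled variance, n per group = [0.64×0.36 + 0.26×0.74] × (1.960 + 1.282)² / 0.38² = 30.8, so 31. The figure reproduces. It is based on an unstratified comparison.

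**2. Analysed size.** The section continues: "Considering a 20% of patients may withdraw from the research, a sample size of 68 will be appropriate". Two sizes are therefore checked: 68 (all infants analysed) and 68 × 0.8 = 54.4, so 54 (20% lost).

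**3. Balance on the stratum.** Each complete block of 2 gives one infant to each arm. Within a birthweight stratum the arms can then differ by at most one infant. The article calls the block sizes variable and prints a single 2. If somewhat larger blocks are also used, the difference is still limited to half a block. A rule triggered by imbalance therefore has almost nothing to detect on this factor.

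**4. Assumptions not in the documents.** 40% of infants are below 1000 g. The odds ratio for the outcome between strata is 2, 3, 6 or 10, the same in both arms. Stratum risks are solved so that each arm has the stated overall risk.

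**5. Type I error by formula.** Take a common risk of 64%. The unstratified test uses V_total = 0.64×0.36 = 0.2304. The variance that actually applies is V_within = 0.4·r₁(1−r₁) + 0.6·r₂(1−r₂), and the error rate is 2[1 − Φ(1.96√(V_total/V_within))].

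- Odds ratio 2: r = 0.733 and 0.578, V_within = 0.2247, error rate 4.7%. The risk-difference interval is √(0.2304/0.2247) = 1.01 times as wide as it need be.
- Odds ratio 10: r = 0.898 and 0.468, V_within = 0.1860, error rate 2.9%. The ratio is √(0.2304/0.1860) = 1.11.

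Simulation at N = 68 gave 5.1% and 3.4%. With a common risk of 45% (midway between 26% and 64%) and odds ratio 10 it fell to about 2%. The stratified test stayed at about 5% throughout.

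**6. Power by simulation.** 40,000 trials per setting, blocks of 2 within stratum, pooled two-proportion test against the Cochran-Mantel-Haenszel test, no continuity correction:

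| Stratum odds ratio | N=68, 64% v 26% | N=54, 64% v 26% | N=68, 64% v 40% |
|---|---|---|---|
| 2 | 0.898 → 0.903 | 0.807 → 0.818 | 0.500 → 0.519 |
| 3 | 0.901 → 0.916 | 0.812 → 0.836 | 0.495 → 0.540 |
| 6 | 0.912 → 0.941 | 0.825 → 0.877 | 0.493 → 0.582 |
| 10 | 0.921 → 0.957 | 0.832 → 0.903 | 0.493 → 0.619 |

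The gains are about 1-4, 1-7 and 2-13 points. The 40% in the last column is an assumed smaller effect.

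**7. Does the conditional rule recover the gain?** A separate simulation used logistic likelihood-ratio tests and three further covariates, each tested for imbalance at 5%. Adjustment was triggered in 13-16% of trials. With N = 68, half the infants below 1000 g and a stratum odds ratio of 10, power was 0.922 unadjusted, 0.922 under the conditional rule and 0.952 with the stratum always included. The rule recovered none of the gain.

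**The case against.** The best defence is that the unadjusted analysis is valid, that the loss at the design effect is small, and that an unseen analysis plan may hold the covariate list, the imbalance criterion and the order of results. The first two points stand and limit the weight of this one. The third stands for the list and the criterion. It does not remove the core, because the article itself states both the unadjusted model and the conditional rule, and an analysis plan that always included the stratum would contradict it.

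Four stronger readings are tempting, and the documents do not support them.

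- *The data choose the primary result.* The text adds an adjusted model after the unadjusted one and does not replace it, and it describes the covariates as fixed in advance. In simulation, even taking the better of the two p-values gave a type I error of 2.8-5.4%. The choice of model changed significance in about 1% of trials at the design effect. The fault is ambiguity, not false-positive inflation.
- *Some imbalance is close to a coin toss.* This needs an assumed significance test and an assumed number of independent variables. The article states neither.
- *Siblings are wrongly treated as independent.* The article says only "Multiple birth infants will be randomized separately", which concerns allocation. The analysis of siblings is not described, and an analysis plan could supply it. Ignoring twin correlation in simulation gave a type I error of 3.9-4.9% and power of 0.89-0.91, so the effect is negligible.
- *All the intervals are too wide.* That holds for the risk difference. For the logistic odds ratio, adjustment enlarges the standard error of the log odds ratio (0.545 to 0.590 at stratum odds ratio 3, 0.544 to 0.658 at 6). Power rises because the adjusted odds ratio lies further from 1.

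**Conclusion.** The point holds as a mismatch between design and analysis with a modest cost. The stated primary analysis omits the stratification factor, the conditional rule will almost never restore it, and no lead result is named. Conclusions would not be invalid; the test errs on the cautious side. The size depends on how prognostic birthweight is and on the share below 1000 g, both assumed here. At a stratum odds ratio of 2 the loss is trivial. It becomes material if birthweight is strongly prognostic together with fewer analysed infants or an effect smaller than the 38 points assumed (64 − 26).

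**What to change.** State one primary analysis that always accounts for birthweight group. A suitable choice is the Mantel-Haenszel risk difference with 95% CI, stratified at 1000 g. It keeps the risk difference already planned. Logistic regression with arm and stratum is an alternative, provided the report notes that the adjusted odds ratio is a different quantity from the unadjusted one and has a wider interval.

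Delete the imbalance condition. Report the unadjusted result as a sensitivity analysis only and, if wished, a variance that is robust to sibling correlation.

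The cost is a few sentences and a few lines of code. No new data are needed, since birthweight is recorded for every infant. The article's Protocol amendments section requires a formal amendment and ethics review for a change to the analyses. It should be made before outcomes are compared by arm.

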**Method:**

A single-center randomized controlled trial will be performed. All eligible infants will be randomized and assigned to either VTV or PCV group with 1:1 ratio using sealed envelopes. Death or BPD at 36 weeks’ postmenstrual age will be used as the primary outcome. Secondary outcomes include BPD, death, length of invasive MV, noninvasive mechanical ventilation, and oxygen use, length of hospital stay, failure of conventional MV, rate of using high-frequency oscillatory ventilation (HFOV) as rescue therapy, rate of reintubation within 48 h, and hospital expenses.

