### Methods in analysis to handle protocol non‐adherence and any statistical methods to handle missing data

Patients with missing outcome data will be censored at last contact. Descriptive statistics on the use of non-protocolized modes as well as intolerance of conventional ventilation mode (duration in days and percentage of time in study spent on HFOV) will be provided.

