## Definitions

Withdrawal: Patients died or were discharged early due to non-respiratory causes (e.g., infectious shock, cardiac insufficiency, new congenital anomalies discovered after inclusion in the study, family wishes, etc.). All withdrawn patients need to record the specific reason for withdrawal.

Lost to follow-up: Difficult to follow-up after discharge due to family wishes or loss of contact information.

Discontinuation: Patients requiring higher respiratory support/ECMO due to difficulty maintaining oxygenation with the ventilator parameters established by protocol; all patients discontinuing the study should be evaluated by the attending, and the specific reasons and ventilator parameters should be documented by the investigator.

Adverse events/side effects: adverse events that may be caused by the intervention, such as air-leak syndrome, ventilator-associated pneumonia (VAP), and unplanned extubation. We will report all adverse events. If patient diagnosed with air-leak syndrome after enrollment, we will evaluate placing a chest tube depend on the hospital protocol. If unplanned extubation happened, we will evaluate patient’s respiratory condition to decide whether reintubate or not. If an adverse event such as unplanned extubation or pneumothorax occurs leading to early termination of the patient from the study, we will report the percentage of occurrence.

All predictable adverse events and adverse events need to be listed in the informed consent form and explain to the family. Unpredictable adverse events/adverse events need to be communicated to the family promptly after they occur and consent to continue the study. The occurrence of adverse events/adverse reactions needs to be judged by the attending whether to continue the current study and documented by the investigators to discuss whether the cause of occurrence is due to the study protocol for subsequent improvement.

Partially predictable adverse events are listed in the secondary outcomes.

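### The Hodges-Lehmann comparison is given an interquartile range where a 95% confidence interval belongs, and the rules for deaths in the duration outcomes do not fit together

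*Protocol article*

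**What the plan says.** The Statistical methods section gives two options for continuous outcomes. One is a difference in means with a 95% CI from the t-test. The other is "mean differences with P25-P75 (using Hodges-Lehmann) will be also calculated for continuous outcomes". Linear regression supplies adjusted differences if needed. Risk differences and odds ratios for binary outcomes also carry 95% CIs, so the nonparametric option is the only one without a confidence interval. The section does not say which continuous outcomes use which option.

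The duration outcomes, listed in the Abstract and under Secondary outcome, are "length of invasive MV, noninvasive mechanical ventilation, and oxygen use", and length "of hospital stay".

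Three statements bear on how an infant who dies enters them:

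- Statistical methods: "All efficacy analysis will be conducted on an intention-to-treat basis".
- The section on non-adherence and missing data: "Patients with missing outcome data will be censored at last contact".
- Definitions, where withdrawal begins: "Patients died or were discharged early due to non-respiratory causes".

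**The concern.** Two things are wrong with the nonparametric option as written. The estimator is misnamed, and the interval beside it does not measure precision. Durations of support and stay are usually skewed, so they are the outcomes most likely to be sent to this option. A reader who takes P25-P75 for an error bar would conclude that the trial says almost nothing about duration, even where the data are informative.

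The second, smaller matter is deaths. The trial aims to reduce mortality, so the arms may differ in it. None of the three named methods (t-test, Hodges-Lehmann, linear regression) can use a censored value, and it is not stated whether an infant classed as withdrawn because of death stays in the duration comparison.

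**Working it through.** **Inputs.** The trial size is 68 infants in a 1:1 ratio (Sample size; allocation section), so 34 per arm. The document gives no distribution of durations, no mortality rate and no timing of deaths. Everything of that kind below is an assumption. The document states no figure for the duration outcomes, so there is none to reproduce.

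**1. Width.** Simulation with no true difference. P25-P75 is taken over all pairwise between-arm differences, and the 95% CI is the rank-based Hodges-Lehmann interval.

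| Assumed durations | Per arm | P25-P75 width (days) | 95% CI width (days) |
|---|---|---|---|
| Lognormal, median 10, log-SD 0.9 | 34 | 17.1 | 8.1 |
| same | 200 | 16.8 | 3.0 |
| Lognormal, median 7, log-SD 1 | 34 | 13.5 | 6.2 |
| same | 136 | 13.2 | 2.8 |

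At 34 per arm the ratio is 17.1/8.1 = 2.1 or 13.5/6.2 = 2.2. The confidence interval narrows with sample size and P25-P75 does not.

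**2. How often it spans zero.** This needs no distributional assumption beyond the absence of ties. P25-P75 of the pairwise differences lies wholly on one side of zero only if about 75% or more of the pairs favour one arm. With no difference, the proportion of pairs favouring one arm has mean 0.5 and SD √[(m+n+1)/(12mn)]. With m = n = 34 this is √[69/(12 × 1156)] = 0.0705.

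- P25-P75 excludes zero at a departure of 0.25, and 0.25/0.0705 = 3.54 SD, a two-sided P of about 0.0004.
- The 95% CI excludes zero at a departure of 1.96 × 0.0705 = 0.138.

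The simulations agree: P25-P75 covered zero in over 99.9% of runs without an effect, and the 95% CI in 95.0% (median 7, log-SD 1).

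**3. Disagreement with the P value.** Suppose the true duration is halved (medians 3.5 and 7 days, log-SD 1, 34 per arm). The 95% CI excluded zero in 79% of runs and P25-P75 in 17%. The CI lies inside P25-P75 at this size, so in about 79 − 17 = 62% of runs a significant rank test would stand beside an interval spanning zero. A larger trial would not cure this: the true proportion of pairs favouring the shorter arm is Φ(ln 2/√2) = Φ(0.490) = 0.69, below the 0.75 needed.

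**4. Deaths, if entered with their observed durations.** With no effect among survivors, the difference in means (lower-mortality arm minus higher-mortality arm) is

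(difference in mortality) × (mean duration in survivors − mean duration in infants who die).

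- *Hospital stay:* survivors' mean assumed 60 days, deaths on days 1-14 (mean 7.5), mortality 10% vs 20%. 0.10 × (60 − 7.5) = +5.3 days. Simulation: 5.3 on the mean, 3.4 on Hodges-Lehmann.
- *Invasive ventilation, deaths on days 1-7 (mean 4):* survivors' median 10, log-SD 0.9, so mean 10 × exp(0.9²/2) = 15.0. Mortality 10% vs 25%. 0.15 × (15.0 − 4) = +1.6 days. Simulation: about +1.7 on the mean, +1.1 on Hodges-Lehmann.
- *Invasive ventilation, deaths on days 7-28 (mean 17.5):* 0.15 × (15.0 − 17.5) = −0.4 days. Simulation: about −0.4 on the mean, −0.8 on Hodges-Lehmann.

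The bias exists under this reading, but its sign for invasive ventilation turns on when infants die.

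**The case against.** The strongest reply has four parts.

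- **Scope.** P25-P75 belongs to one option only, and the document does not assign the durations to it. This stands. The error is in the wording of that option, whichever outcomes use it.
- **Inference.** Significance is judged by P < 0.05, so a wide descriptive interval does not change a decision. This also stands, but it leaves the estimate without a measure of precision and allows the conflict shown in step 3.
- **Meaning.** P25-P75 might be meant as quartiles within each arm, or as a 50% interval. The sentence attaches it to the difference. Read as a 50% CI, it covered the truth in 49% of runs at 34 per arm (width 2.0 days; median 7, log-SD 1). Neither reading gives a counterpart to the t-test's 95% CI.
- **Deaths.** A reader might infer that early deaths are scored as short durations, so that the arm with more deaths looks better. The document does not say so. It is one reading of intention to treat with the named methods; the censoring sentence and the withdrawal definition allow others, and an analysis plan that is not shown may settle it. Even on that reading the direction is not fixed, as step 4 shows. The Introduction also expects volume-targeted ventilation to shorten ventilation, so the net effect on durations cannot be predicted. This part of the reply is right and limits the point about deaths to a need for reconciliation.

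**Conclusion.** The interval error is certain, because it is in the text and not in an omission: Hodges-Lehmann is not a mean difference, and P25-P75 is not its confidence interval. At 34 per arm the stated interval is about twice as wide as the 95% CI under both assumed lognormal distributions. Without an effect it spans zero almost always, whatever the distribution.

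The point about deaths is conditional. The three statements do not make one rule for the duration outcomes. If observed durations of infants who die are used, unequal mortality can bias the comparison by a few days of hospital stay, or by a smaller amount in either direction for invasive ventilation. These sizes rest on assumed mortality, timing of deaths and survivor durations. The stronger claim, that the plan favours the arm with more deaths, is not supported.

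Only secondary outcomes are affected. The primary outcome includes death, and death is also reported separately, so a mortality imbalance would be visible.

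**What to change.** In Statistical methods, replace the nonparametric wording with: *Hodges-Lehmann median difference with its distribution-free 95% CI*. P25-P75 may stay as a description of each arm beside its median.

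Reconcile the intention-to-treat sentence, the censoring sentence and the withdrawal definition, so that one rule says how an infant who dies enters each duration outcome, and present the durations beside mortality by arm. Several methods could serve: a competing-risk analysis, ranking death as the worst result, or days alive and free of support. The choice is the trial team's. The last of these replaces the listed outcomes and mixes death with duration, so its components would have to be shown beside it.

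No new data are needed. The interval correction is a few words. The Protocol amendments section requires a formal amendment and ethics review for changes to analyses or outcomes. Recruitment has begun, so the change should be made before any comparison by arm is seen.

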### Interim analyses

There are no plans to conduct an interim analysis of the outcomes.

